#### Recruitment of participants on hospital wards

**In General:**

Health-information control group and post-intervention group:Identified through hospital electronic record systems or equivalent to identify if a First Nations child has been admitted with an ALRI.A researcher will invite the parent, while on the ward ***during the child’s admission***, to participate in the study using the following process:Lung health information will be given to parents in a culturally secure way, which includes the use of an information flip chart [27].The study will be explained verbally and via written study information.Parents will be invited to participate in the study (with follow-up) and to consent or opt out of an interview.If consenting, an interview will be conducted.A First Nations researcher will be available for all interactions with First Nations participants.During recruitment, parents will be asked for the best contact number for a follow-up phone call to obtain follow-up data from parents.

#### Recruitment during COVID restrictions

Researcher will access admission records to identify if a First Nations child has been admitted with an ALRI (current protocol).A culturally secure information pack complete with an information pamphlet (see attached information pamphlet_COVID-19_ V3-03042020) explaining lung health and acute and chronic chest infections, a brief explanation letter to parents (see Cover Letter for Families_COVID-19_V3_03042020), the study information sheet and consent form will be left at the door outside patient rooms in a clearly marked folder/envelope.The researcher will send a text message (attached Recruitment Text_COVID-19_V1_190320) to the patient’s parent. The text message will have a poster attachment (see attached Recruitment poster_COVID-19_V1_19032020) and (if recipient does not use a smartphone) a short blurb about the study to invite the parent to participate or return text to “opt out”.The researcher will telephone the parent after at least 30 min if no “opt-out” text is returned to provide information and go through the informed consent process. The 30-min opt-out window considers that many patients are admitted overnight only for acute respiratory conditions and are discharged from hospital in the morning after an overnight stay. Thus, the timeframe for recruitment is limited.Parent may give verbal consent or choose to fill out the paper copy they received. The paper copy will be retrieved by the research team.

### Assignment of interventions: allocation

**Sequence generation**

N/A

**Concealment mechanism**

N/A

**Implementation**

N/A

**Assignment of interventions: Blinding**

**Who will be blinded**

N/A

**Procedure for unblinding if needed**

N/A

### Plans for assessment and collection of outcomes

A PC-QoL tool [23] will be administered to eligible participants (not attached here in for copyright reasons, but for tool provided). The PC-QoL tool [23] has eight questions rated on a Likert-scale, and administered using REDCap software. A researcher who is trained and skilled in REDCAP software will create, maintain and enter data onto the database for all sites.

Participants will have their unique medical record unit number attached to their data, so will be re-identifiable. The use of this unique identifier will also allow us to link multiple records for the same participant together, as it is anticipated that a small (but non-negligible) number of participants will have recurrent chronic wet cough and hence be likely to be captured on two or more occasions spanning different data collection periods. The database will be stored on a computer at a location requiring an access card swipe for access. The computer is accessed by a password lock. Participants’ information will only be used for the purposes of this research project and will only be disclosed with permission except where required by law.

It is anticipated that the results of this research project will be published and/or presented in a variety of fora. In any publication and/or presentation, information will be provided in such a way that a participant cannot be identified. Confidentiality will be maintained by removing all the identifiers and using the participant’s code number for data presentation.

The study team collecting data will be comprised of at least two individuals at each site, the First Nations research officer and clinician researcher. The clinician research lead, i.e., project coordinator, will monitor data collection and source documents during regular study meetings. Once a month, the project coordinator will verify the information that has been collected on the study database and monitor any missing data or errors in data entry. If regular errors in data entry or collection are noted, an action plan will be put in place.

All eligible participants will be included in the study. All researchers recruiting participants and collecting data will have a current Good Clinical Practice certification.

### Plans to promote participant retention and complete follow-up

Retention of participants for the 6–12-week follow-up phone call will be primarily achieved by ensuring the best contact number is provided by the parent at time of recruitment. In addition, if the parent does not answer the call, an SMS text will be sent to explain to the parent what the call is about. Lastly, the phone used to text and call the patient is from a visible (unblocked) number. Parents have suggested these steps to improve family engagement with follow up phone calls.

### Data management

Study data will predominantly come from two sources, (i) clinical care/medical records, and (ii) primary data collection, the latter of which will be entered directly into the study database. The researcher will utilise a REDCap (https://www.project-redcap.org/) database. REDCap is a secure, web-based, electronic data capture platform. The instance of REDCap that will be used is hosted on Telethon Kids Institute servers (within Western Australia), which are encrypted, behind multiple firewalls, contain intrusion detection systems in place, and are periodically backed-up (offsite, still within Western Australia) in line with institute policy. This permission restricted, web-based electronic data capture platform meets the recommendations of the Australian Clinical Data Interchange Consortium.

We will follow a formalised data management plan that details all clinical data to be regularly (fortnightly, minimum) entered on REDCap, with quality control reviews to be carried out monthly. A data audit will be completed by research staff to query missing entries. Unvalidated data will be excluded from analysis. Repeated data errors or omitted data will be investigated and resolved. The REDCap platform provides quality control functionality including data range and consistency checks. The use of REDCap ameliorates the risk of media obsolescence as data can be exported in a wide variety of formats.

Data entered into the REDCap database will be consistent with and substantiated by the patient’s medical record and other original source documentation. Source documentation will be legible, complete and attributable to an originator. The analysis of all collected data will be carried out by the study team. The study team directly collecting the data will be comprised of at least two individuals per site: the Aboriginal research officer and a second research officer. The project coordinator will monitor data collection and source documents during regular study meetings.

### Confidentiality

Participant identification will occur via daily audit of hospital admissions only accessed by a hospital respiratory clinician or paediatrician who would ordinarily have access to these data for clinical reasons, to protect patient confidentiality. The patient’s name and ward will be given to the research assistant who will visit the participant and provide information about the study. No data will be collected on the participant without informed consent. If a participant refuses consent, no data will be collected with exception that there was an admission where study consent was refused.

Once informed consent is obtained then standard data will be collected as per the protocol. Data will be collected from the participants, discharge summaries and the hospitals admissions database (e.g., iSoft).

Any written materials will be securely stored in a locked office with authorised access by swipe card only, in compliance with the Telethon Kids Institute Research Data Confidentiality policy. The data will be stored for a minimum of 15 years as per the NHMRC Guidelines.

**Plans for collection, laboratory evaluation and storage of biological specimens for genetic or molecular analysis in this trial/future use**

N/A

### Statistical methods for primary and secondary outcomes

Data will be exported from REDCap and processed into the form of one record per participant per visit. Basic descriptive statistics will be used to describe and characterise the data, including reporting means and standard deviations, medians and interquartile ranges, and counts and percentages, as appropriate.

The primary analysis for the study will be carried out using a mixed model framework. The primary outcome variable will be the absolute PC-QoL score; with the difference between the “nil-intervention” and the “post-intervention” groups being the value of interest. This value will be estimated by the coefficient of a 2-level fixed term from the model that indicates the “nil-intervention” and “post-intervention” groups of the study; it is this coefficient (and the accompanying two-sided 95% confidence interval) that will be reported as the main outcome of the study. This coefficient represents a ‘whole of program’ effect (difference between the nil-intervention and post-intervention groups). The model, at a minimum, will include both a fixed and random term for study site (to control for both the within site clustering and within person clustering, as we anticipate a number of participants may present in multiple observation periods) and will include the covariates of calendar week (to control for time and seasonal effects), sex (to control for risk differences by sex), and age (to control for risk differences by age). Adjusted analyses, such as that proposed, typically increases study power [28]. Model fit statistics and graphics will be examined. If a different model is deemed to provide a better fit than that described above, rationale to support this will be provided in the report.

Additional analysis of the primary outcome will be carried out, including a minimally adjusted model (using the same framework as described above, but with no covariates in the model, only within site clustering) and a non-adjusted model (using Student’s t-test). Basic comparisons for second outcome measures will utilise Chi-squared tests and Student’s t-tests (with comparison made between nil-intervention and health-information only data, health-information only and post-intervention, and nil-intervention and post-intervention data). In line with the primary outcome analysis, a mixed model framework will be used to examine the effect of prognostic factors of interest on binary (logistic) and count (Poisson) outcomes, where intervention-stage effects will be reported with 95% confidence intervals. A significance level of 0.05 will be used to determine statistical significance, though the focus on the analysis and reporting will be on the effect size estimates and their associated confidence intervals.

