### Health outcome/primary outcome measure (Quality of Life (PC-QoL))

The primary outcome is the parent-proxy Cough-specific Quality of Life (PC-QoL) for children with chronic wet cough. Effective follow-up and management of children hospitalized with ALRIs will be assessed by measuring PC-QoL between 6 weeks and 3 months after hospitalization. We will use the 8-item version of the PC-QOL tool that has been shown to be a valid, reliable, and responsive tool for measuring the burden of chronic cough in children. This tool has been used effectively in First Nations settings [17, 18].

Rationale: children with ongoing respiratory symptoms and cough post hospitalization will have improved quality of life if they receive effective medical follow-up at one-month post discharge. The PC-QoL scores will be compared pre and post implementation in different children who had a chronic wet cough post-discharge. Children with chronic wet cough post-hospitalization who received timely follow-up and optimal management will have better cough specific QoL than children who did not. It has been determined, using the anchor method, that 0.9 is the calculated minimum important difference in PC-QOL [23].

Respiratory symptoms after ALRI should typically resolve within 4 weeks. Children with ongoing wet cough 4 weeks post-hospitalization are likely to have protracted bacterial bronchitis that should resolve if detected and managed in a timely way. Hence, if children receive appropriate follow-up and management a month after discharge then we expect their cough related QoL to be better after 6–12 weeks than those who did not (waiting 6–12 weeks allows time for management to be completed in those children with chronic wet cough who may require up to a month of antibiotic treatment).

The PC-QoL tool will be administered by a research officer in-person at the hospital sites, over the phone, or electronically (online option via REDCap for those participants who would prefer this option). Participants will be contacted by the research officer via text message or telephone.

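### The primary model claims that site terms control within-person clustering, but no child-level term is named and the random site term is redundant beside the fixed one

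*Protocol article*

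**What the plan says.** The section on statistical methods for primary and secondary outcomes sets out the primary mixed model. The result to be reported is the coefficient comparing nil-intervention with post-intervention, with its two-sided 95% confidence interval. For clustering, the model "will include both a fixed and random term for study site (to control for both the within site clustering and within person clustering", and the reason given is "as we anticipate a number of participants may present in multiple observation periods". Data are to be "processed into the form of one record per participant per visit", so a child can contribute more than one row. The listed terms are described as a minimum, and the section adds: "If a different model is deemed to provide a better fit than that described above, rationale to support this will be provided in the report". The minimally adjusted model that follows accounts for clustering within site only.

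The section on assessment and collection of outcomes says that "it is anticipated that a small (but non-negligible) number of participants will have recurrent chronic wet cough", captured in more than one data collection period, and that the identifier "will also allow us to link multiple records for the same participant together". The section on the primary outcome measure describes the comparison this way: "The PC-QoL scores will be compared pre and post implementation in different children who had a chronic wet cough post-discharge".

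**The concern.** There are two separate faults in one sentence.

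First, the sentence assigns both the fixed and the random term to study site and says that together they deal with within-person clustering. Site effects absorb what children at one site share. They say nothing about what two records from one child share beyond that. With no term for child, repeat records enter as independent once site and the covariates are accounted for, so the model lacks a property that the article says it has.

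Second, once each site has its own fixed effect, a random intercept for the same sites has nothing left to describe, so its variance cannot be estimated from the data.

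What is at stake is the width of the interval reported as the main result, and whether the primary model can be fitted as specified without a change made after the data are in.

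**Working it through.** **Plan's own figures.** The article gives no figure for the share of repeat children or for the within-child correlation, so there is nothing to reproduce on this point. The powers in the sample size section do reproduce with SD 1.3:
- 12 per period at a single site, difference 1.6: 82.1% (stated above 80%).
- 4 clusters of 5 per period, difference 1.6, design effect 1.061: 95.7% (stated above 95%).
- 4 clusters of 10 per period, difference 0.9, design effect 1.132: 82.0% (stated above 80%).

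None of them uses a within-child correlation, so none changes here.

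**Redundant site term.** A random site intercept lies in the space spanned by the site dummies. This was checked on simulated data with 4 sites, 10 records per site per period and SD 1.3:
- With fixed site effects plus a random site intercept, the REML log-likelihood was -54.984419 at every site variance tried (0, 0.1, 0.5, 2, 10 and 100).
- The period coefficient (1.309431) and its standard error (0.290689) were the same at every value.
- Under maximum likelihood, the log-likelihood fell steadily from -48.8069 at variance 0, so the estimate goes to 0.
- With the fixed site effects removed, the REML profile was curved, and the value at 0.1 (-55.2648) exceeded that at 0 (-56.6053).
- On a second simulated data set, a standard mixed-model routine returned a site variance of 2.01 with a warning that the Hessian was not positive definite. Its period effect (1.4256) and standard error (0.3169) equalled those from least squares with site dummies.

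**Missing child term.** Let each compared stage have n records with variance σ², let s be the share of records from repeat children, and let r be the correlation between two records of one child.

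- *Repeats in both compared stages.* The covariance of the two stage means is s·r·σ²/n. The variance of the difference is therefore (2σ²/n)(1 − s·r). A model that ignores this uses 2σ²/n, so model SE / true SE = 1/√(1 − s·r).
- *Repeats as pairs within one stage.* Each stage mean has variance (σ²/n)(1 + s·r), so model SE / true SE = 1/√(1 + s·r).

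With r = 0.5 (assumed) and repeats spanning the compared stages:

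| s (assumed) | 1/√(1 − s·r) | Model SE |
|---|---|---|
| 0.05 | 1/√0.975 = 1.013 | 1.3% too large |
| 0.10 | 1/√0.95 = 1.026 | 2.6% too large |
| 0.20 | 1/√0.90 = 1.054 | 5.4% too large |

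For contrast, pairs within one stage at s = 0.20 give 1/√1.10 = 0.953, a standard error 4.7% too small.

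Simulation under the null (20,000 trials per scenario, fixed site effects, no child term) agrees in direction. With repeats in both periods, shares of 10 to 40% and correlations of 0.3 to 0.7, the average model SE was about 0.29 against a true 0.286 down to 0.249, and the type I error was 4.8% down to 2.3%. With 20 to 40% of records in same-period pairs, the true SE was 0.30 to 0.32 against about 0.29, and the type I error was 5.8% to 8.1%.

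**The case against.** The best defence is that this is a drafting slip. The parenthesis names two purposes and the sentence names two terms, so the authors may have meant a fixed effect for site and a random effect for participant. The intention to handle repeats is explicit, "The use of this unique identifier will also allow us to link multiple records for the same participant together", and the exact random-effects structure often sits in an analysis plan. Much of this stands, and it argues against reading a serious design error into the text. It does not rescue the sentence: the wrong term is in the minimum set, and the better-fit clause leaves the correction until outcomes are known.

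It is also fair to say that the numerical effect is small. The article expects few repeats. The primary contrast has two levels, so a child who recurs only between the health-information stage and another stage adds no pair to it. A contributing child must have chronic wet cough in both compared stages.

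A child intercept has its own weakness, because it would rest on very few pairs. With 20 records per stage (the aim in the section on pragmatic data collection), 5 to 20% of children in both stages and correlation 0.3 to 0.5, its variance was estimated at zero in about 15 to 31% of simulated trials. The fix therefore needs a stated fallback.

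Three stronger readings are tempting and are not supported:
- *The over-parameterised site term damages the primary result.* It does not; the stage coefficient and its standard error are unaffected. Nor does it cause repeats to be treated as independent, which follows only from the absence of a child term.
- *The trial will produce too many false positives.* That requires repeats within one stage. The article anticipates repeats across periods, for which the interval is conservative.
- *The reference to different children contradicts the expected repeats.* It is better read as loose wording for an unpaired comparison between groups, with no effect on the analysis.

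**Conclusion.** The point holds in a limited form. The claim that site terms control within-person clustering is wrong as written, and the model named does not account for repeat children. For the anticipated pattern, the cost is an interval modestly too wide: the SE is about 1 to 3% too large at 5 to 10% repeats and about 5% at 20%, with correlation 0.5. The repeat share and the correlation are assumptions, since the article gives neither. Same-stage repeats would reverse the direction, and the article does not exclude them. The redundant random site term is a separate fault whose practical cost is a singular fit or a meaningless site variance. This should be fixed because it concerns the primary model and the correction is simple, but the numerical effect does not justify a higher grade.

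**What to change.** Reword the clustering sentence so that the primary model has study site as a fixed effect and, in place of the random term for site, a random intercept for child defined by the linked identifier. Add a fallback, for example that the child term is dropped if its variance is estimated at zero. Delete the statement that a site term controls within-person clustering. A particular small-sample degrees-of-freedom method is optional and can be left to the analysis plan.

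The cost is a sentence or two in the statistical methods. No new data are needed, because the identifier is already collected, and no stated power figure changes.

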## Methods

### Trial design

The study is a multi-centre, pseudo-randomized stepped wedge design where the medical follow-up strategy at each study site is implemented with consideration of barriers and facilitators using a combined Participatory Action Research (PAR) and implementation science approach, guided by the Consolidated Framework of Implementation Research. Outcome data for each site will be collected in three stages, as discussed below. The timing of interventions at individual study sites/cluster will not be randomised but determined by site-related logistics which will vary greatly (months to years) between sites (Fig. 1).

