### Sample size

The primary outcome measure for this trial is the PC-QOL (8-item version). There is limited data available to inform a robust sample size calculation and it is acknowledged that there are challenges with estimating potential cohort sizes within the limited remote communities included in this study, thus a pragmatic approach has been taken to the sample size calculations. Data (unpublished) from our previous studies using the PC-QOL suggests a conservative standard deviation of 1.3, a historic mean score of approximately 2.7, a pre-implementation mean score of approximately 3.6, and a post-implementation mean score of approximately 4.3. Two calculations were carried out, one based on a two-sided T-Test (to reflect an examination of the intervention effect within a single site), and the other based on the overall analysis (reflecting the clustered, within site, nature of the data).

Single site analysis with at least 12 participants with chronic wet cough in each period will have > 80% power to detect a nil-intervention (2.7) v post-intervention (4.3) difference of 1.6, alpha 0.05. Full sample (clustered) analysis with at least 5 participants per cluster (4) per period (assuming COV 0.65, ICC 0.01) will have > 95% power to detect a nil-intervention (2.7) v post-intervention (4.3) difference of 1.6, alpha 0.05; at least 10 participants per cluster (4) per period will be required to have > 80% power to detect a difference of 0.9 (alpha 0.05). Adjustments for multiple comparisons were not made as calculations are to provide guidance only, with final sample size being dependent on cohort sizes and diagnosis counts during observation periods; sample size calculations were carried out using PASS [26].

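### The stated power is for a comparison with no time term, but the primary model must contain calendar week; one week term cannot deliver both that power and control of time

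*Protocol article*

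**What the plan says.** Under Statistical methods for primary and secondary outcomes, the main result is the coefficient of a two-level nil/post term. The minimum model has fixed and random site terms, age and sex, and it "will include the covariates of calendar week (to control for time and seasonal effects"). The same paragraph adds: "Adjusted analyses, such as that proposed, typically increases study power".

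Under Sample size there are two calculations: "one based on a two-sided T-Test" for a single site, and "the other based on the overall analysis (reflecting the clustered, within site, nature of the data"). The planning data, it says, "suggests a conservative standard deviation of 1.3". The clustered claims are power above 95% for 1.6 with "at least 5 participants per cluster (4) per period", and above 80% for 0.9 with 10 per cluster per period. The listed inputs are means, SD, cluster-size COV 0.65, ICC 0.01 and alpha. No time term appears.

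Under Eligibility criteria, nil children were admitted between 6 weeks and 6 months before the trial starts, and post children from the first day of implementation. Under Trial design: "The timing of interventions at individual study sites/cluster will not be randomised but determined by site-related logistics", with variation of months to years between sites.

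**The concern.** At any one site every nil child precedes every post child, with the health-information stage between them. Once site is a fixed effect, a common linear week slope is estimated only from within-site variation, and there elapsed week and the nil/post indicator carry almost the same information. Staggered site starts do not help by themselves, because the site terms absorb them. Only differences between sites in the nil-to-post gap, or long recruitment windows, separate the two.

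The adjustment would then widen the interval for the main coefficient, the opposite of what the power sentence suggests. If week is read as week of year, the precision largely survives, but a before-after contrast is left exposed to secular change although the covariate is said to control time. At stake is whether the stated power describes the analysis that will give the main result.

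**Working it through.** **1. Reproduce the stated power (no time term).** Inputs from Sample size: SD 1.3, COV 0.65, ICC 0.01, 4 clusters, alpha 0.05 (two-sided assumed for the clustered case).

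Design effect DE = 1 + ((COV² + 1)m − 1) × ICC; effective n per stage = 4m/DE; SE = 1.3 × √(2/n).

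- m = 5, difference 1.6: DE = 1 + (1.4225 × 5 − 1) × 0.01 = 1.061; n = 20/1.061 = 18.8; SE = 0.423; 1.6/0.423 = 3.78; power 96.6% (normal) or 95.7% (t, 38 df).
- m = 10, difference 0.9: DE = 1.132; n = 35.3; SE = 0.309; ratio 2.91; power 82.9% or 82.0%.
- Single site, 12 per period: 82.1% (t).

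All three claims reproduce, without any time covariate.

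**2. How collinear is elapsed week with stage?** The nil window is weeks −26 to −6 from trial start (protocol). The gap from trial start to implementation and the length of the post period are not given, so they are assumptions.

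Take a 26-week gap and a 26-week post period, with uniform admissions. The window centres are −16 and 39, which is 55 weeks apart. The between-group variance of week is (55/2)² = 756. The mean within-group variance is (20²/12 + 26²/12)/2 = 44.8. So R² = 756/(756 + 44.8) = 0.94. In small samples, with site terms fitted, it averages 0.95.

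The variance of the nil/post coefficient is multiplied by 1/(1 − R²). At R² = 0.951 that is 20.4, and the SE becomes 0.41 × √20.4 ≈ 1.86.

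**3. Power with linear elapsed week.** Four sites with fixed site terms, starts staggered by 26 weeks, equal site sizes, two-level stage term; averages over 400 random draws of admission dates per calendar; noncentral t.

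| Gap by site (weeks) | Post period (weeks) | R² | SE, 20 per stage | Power for 1.6, 20 per stage | Power for 0.9, 40 per stage |
|---|---|---|---|---|---|
| No time term | – | 0 | 0.41 | 97% | 86% |
| 52 at all | 26 | 0.98 | 2.71 | 9% | 8% |
| 26 at all | 26 | 0.95 | 1.88 | 13% | 11% |
| 52 at all | 52 | 0.95 | 1.90 | 13% | 11% |
| 26 at all | 52 | 0.91 | 1.40 | 21% | 16% |
| 26, 39, 65, 104 | 52 | 0.88 | 1.22 | 25% | 19% |
| 26, 39, 65, 104 | 26 | 0.88 | 1.19 | 26% | 19% |
| 13, 26, 52, 104 | 52 | 0.83 | 1.01 | 34% | 24% |
| 13, 26, 52, 104 | 26 | 0.81 | 0.96 | 37% | 26% |
| 13 at all | 104 | 0.80 | 0.94 | 39% | 29% |
| 13, 26, 104, 156 | 52 | 0.78 | 0.88 | 43% | 30% |
| 13, 26, 104, 156 | 26 | 0.75 | 0.83 | 47% | 33% |

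The 86% in the first row exceeds the 82.9% of step 1 because fixed site terms remove the ICC and site sizes are equal. For 0.9, six of the eleven calendars give roughly 11–24%; the extremes are 8% and 33%. Using health-information records with a three-level stage term gives 19–57% for 1.6.

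At 20 per stage the 95% half-width is 2.03 × SE, from 2.03 × 0.83 = 1.7 to 2.03 × 2.71 = 5.5. The protocol's minimum important difference is 0.9.

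**4. Week of year instead.** Entered linearly, week of year gives power for 1.6 of about 82–97% in most calendars. The exception is when all sites start at the same time of year and the nil and post windows fall in opposite seasons. With a 52-week gap and a 26-week post period this gave 33–44% for some start dates. In no case does the term represent change from one year to the next.

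**The case against.** The sample-size section calls its calculations guidance only, and the figures are correct for what they describe. A model without covariates and a t-test are planned as additional analyses, so the powered comparison will be reported. How week is coded may properly be left to an analysis plan that is not shown. The sentence on adjustment is hedged and covers age and sex as well.

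These points soften the matter but do not remove it. Pragmatic data collection rests feasibility partly on this calculation, and the adjusted coefficient is named as the main outcome. Coding detail can wait, but the protocol itself states the purpose of the term, the power and the direction of the effect on power.

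Three stronger readings are tempting and are not supported:

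- **A single collapsed figure, such as 13–25%.** This needs near-common gaps at every site. The protocol says timing varies greatly, and unequal gaps recover part of the loss. With site random only and staggered starts, power for 1.6 would be about 46–93%, but the model specifies a fixed site term too.
- **That the primary interval must be unusable.** This follows only under elapsed-week coding, which the protocol does not state.
- **That seasonal terms should simply replace the time term.** They leave secular change uncontrolled, which is the weakness of week of year. Choosing between them trades bias against precision, and either choice can be defended if it is made in advance.

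**Conclusion.** The point holds in a bounded form. The stated power figures are right for a two-group comparison without time and do not apply to a primary model that controls elapsed time. Under linear elapsed week and fixed site terms, every calendar tried falls far below the stated power: about 9–47% against above 95% for 1.6 (up to about 57% with health-information records), and roughly 11–24%, with extremes of 8% and 33%, against above 80% for 0.9.

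These ranges rest on assumed gaps of 13–156 weeks and post periods of 26–104 weeks; the protocol gives neither. Under week of year most of the power is usually kept, but the stated control of time is not achieved. The general sentence on adjustment and power is wrong for an elapsed-time covariate in this design, though it may hold for age and sex.

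**What to change.** - Restate the power under Sample size for the model that will be fitted, as a range under stated stage-timing assumptions, with and without elapsed time.
- Delete the sentence on adjustment increasing power, or limit it to covariates that are not aligned with stage.
- Separate season (for example annual sine and cosine terms for week) from elapsed time (weeks from a common origin). Name in advance which is in the primary model, and report the other specification as a named sensitivity analysis. Use all three stages for the elapsed-time model.
- If elapsed time is left out of the primary model, say that the nil/post estimate is a before-after difference not protected against secular change.

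The cost is wording and a rerun calculation; Trial status says recruitment has not begun. The downside is that the stated power will look less favourable and the elapsed-time estimate will be imprecise.
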